Induction of labour is indicated for a variety of clinical reasons, but overall is considered when the outcome for the baby, mother or both will be better if achieving a more imminent vaginal delivery compared to awaiting the spontaneous onset of labour (5). However, induction does not come without risks. It is known to be associated with an increased rate of assisted vaginal delivery, increased epidural rate and can impact upon on the birth experience of the woman (1, 6). More importantly, almost 20% of inductions do not result in a vaginal birth and require an unplanned caesarean section which in itself has additional maternal and neonatal risks, as well as an increase in cost and use of healthcare resources (7, 8). A reliable prediction model to determine which women will successfully achieve a vaginal delivery following induction of labour will allow more informed, shared decision making regarding the risks of induction against the likelihood of achieving a vaginal delivery, taking into consideration the indication for induction and its timeframe.

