**6.2 SAMPLE SIZE**

LWH has 14 available induction of labour appointments available per day for both inpatient and outpatient inductions. We anticipate at least 50% of patients attending to meet eligibility for this study. We hope to achieve a recruitment rate of 50% from this patient group. Over a 12-month period, we would therefore conservatively expect to recruit 100 women.

As this is an exploratory piece of work a formal sample size calculation has not been performed.

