**6.5 STATISTICAL METHODOLOGY**

Descriptive statistics will be generated and presented as means (SD), median (IQR) and frequency of observations (percentages) with 95% confidence intervals as appropriate.

Reliability assessment of the Pregnolia System using Cronbach’s alpha and descriptive statistics with 95% confidence intervals will inform best use of the triplicate CSI measurements. Specifically exploring whether the first, average, median or lowest measurement of the three readings should be utilised in further analysis and most importantly inform best use of the CSI results in clinical practice.

Diagnostic performance of cervical stiffness assessments using the Pregnolia System for IOL outcome will be demonstrated through receiver operating characteristic curves with area under the curve and 95% confidence intervals being calculated, as well as aiming to define the optimum cut-off value for predicting vaginal delivery.

Multivariate analysis will be performed using logistic regression, including CSI and other variables related to IOL outcome, such as maternal age, gestational age and maternal weight at booking(28). Results will be presented as odds ratios with 95% confidence intervals.

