**6.5.1 Participant Groups for Analyses**

Entire observational cohort of 100 women with singleton pregnancies undergoing induction of labour.

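### The optimum CSI cut-off is to be found in the same 100 women, so it will be unstable, and any sensitivity and specificity quoted at it will be optimistic

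*Protocol*

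**What the plan says.** Section 6.5 plans ROC curves for CSI with the AUC and 95% confidence intervals, "as well as aiming to define the optimum cut-off value for predicting vaginal delivery". It does not say what makes a cut-off optimum. It then states: "Multivariate analysis will be performed using logistic regression, including CSI and other variables related to IOL outcome". Maternal age, gestational age and maternal weight at booking follow as examples, introduced by *such as*, and the model's results are to be odds ratios with 95% confidence intervals.

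Section 6.5.1 gives one analysis group: "Entire observational cohort of 100 women with singleton pregnancies undergoing induction of labour". There is no split sample and no second cohort, and section 6.5.3 prescribes complete cases. On size, section 6.2 states: "As this is an exploratory piece of work a formal sample size calculation has not been performed". The Background in section 1 says that "almost 20% of inductions do not result in a vaginal birth". Section 6.5.2 sets no significance level and uses confidence intervals to show precision only. The first objective in section 2 is to inform the design of a powered study.

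**The concern.** A cut-off picked because it separates the outcomes best in one sample fits the chance features of that sample. Sensitivity and specificity computed at that cut-off in the same women are then too good on average, and the cut-off itself moves a good deal from sample to sample. The smaller outcome group governs both effects, and here that group is the women without a vaginal birth.

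The study exists to inform a later powered study. A threshold, or a sensitivity and specificity, taken from these data without correction would give that study an unreliable cut-off and too favourable a starting assumption. An ordinary confidence interval computed at the chosen cut-off does not show this, because it treats the cut-off as if it had been fixed in advance.

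**Working it through.** **Where 100 comes from.** Section 6.2 gives daily capacity ("LWH has 14 available induction of labour appointments available per day"), the eligible share ("We anticipate at least 50% of patients attending to meet eligibility for this study") and a hoped-for recruitment rate of 50%. These give 14 × 0.5 × 0.5 × 365 = 1,277.5 women a year. The protocol then states: "Over a 12-month period, we would therefore conservatively expect to recruit 100 women". So 100 is a recruitment expectation, with no link to the precision of a cut-off.

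**Size of the smaller group.** At 20%, 100 × 0.20 = 20 non-vaginal births (95% binomial range 12 to 28). At 30% there are 30 (range 21 to 39). The 20% is the Background rate for inductions in general, and the 30% is an assumption.

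**Cut-off.** Assume CSI is normal with SD 1 in both outcome groups and that a stiffer cervix favours non-vaginal birth. For a true AUC of A, the group means differ by d = √2 × Φ⁻¹(A), the best cut-off is d/2, and the best attainable J (sensitivity + specificity − 1) is 2Φ(d/2) − 1. For A = 0.7: d = 1.414 × 0.524 = 0.742, d/2 = 0.37 and J = 2 × 0.6446 − 1 = 0.289. In 4,000 simulated studies of 100 women, the cut-off with the largest J was chosen and then assessed in the population:

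| True AUC | Non-vaginal births | J in the study | True J at that cut-off | Overstatement | 95% range of cut-off (SD) |
|---|---|---|---|---|---|
| 0.5 | 20 | 0.145 | 0.000 | 0.145 | −1.90 to 1.88 |
| 0.6 | 20 | 0.263 | 0.122 | 0.141 | −0.99 to 1.43 |
| 0.7 | 20 | 0.389 | 0.265 | 0.124 | −0.46 to 1.29 |
| 0.8 | 20 | 0.530 | 0.423 | 0.107 | −0.07 to 1.36 |
| 0.5 | 30 | 0.129 | 0.000 | 0.129 | −1.89 to 1.94 |
| 0.6 | 30 | 0.238 | 0.122 | 0.116 | −0.98 to 1.36 |
| 0.7 | 30 | 0.371 | 0.267 | 0.104 | −0.46 to 1.22 |
| 0.8 | 30 | 0.516 | 0.426 | 0.090 | −0.04 to 1.31 |

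With 20 births the range is 1.43 + 0.99 = 2.42 SD wide at AUC 0.6, 1.29 + 0.46 = 1.75 SD at 0.7 and 1.36 + 0.07 = 1.43 SD at 0.8. At 0.65 it is about 2 SD. Most of the overstatement falls on the smaller group. At AUC 0.7 with 20 births, sensitivity for non-vaginal birth is 0.72 in the study and 0.62 in truth, and specificity is 0.67 and 0.65. If vaginal delivery is taken as the positive outcome, the two labels swap.

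**AUC of CSI alone.** In the same simulations the mean apparent AUC was 0.499, 0.604, 0.701 and 0.799 for true values of 0.5, 0.6, 0.7 and 0.8, so there is no inflation. The limitation is precision. The Hanley–McNeil variance is [A(1−A) + (n₁−1)(a−A²) + (n₀−1)(b−A²)]/(n₁n₀), with a = A/(2−A) and b = 2A²/(1+A). For A = 0.7, n₁ = 20 and n₀ = 80 this is [0.21 + 19 × 0.0485 + 79 × 0.0865]/1,600 = 0.0050. The SE is 0.071 and the 95% half-width is 0.138.

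**Logistic model.** The four terms named in 6.5 leave 20/4 = 5 events per term, and ten terms would leave 2. In 1,500 simulated studies with a true CSI odds ratio of 1.65 per SD (log-odds ratio 0.50), three other covariates at 0.3 and 20 expected events, the mean estimated log-odds ratio was 0.546 with 4 terms (9% too large), 0.585 with 8 (17%) and 0.599 with 10 (20%). With four terms and no true CSI effect it was −0.002. The confidence interval's upper limit is about 3.1 to 3.5 times its lower limit, so the bias is small beside the imprecision.

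**The case against.** The best case for leaving the plan alone is that section 6 presents itself as an overview. The criterion for the optimum, internal validation and the estimator are commonly settled in a statistical analysis plan, and none is shown here. The work is exploratory, tests no hypothesis and treats intervals as indications of precision. The protocol does not say that sensitivity and specificity at the cut-off will be reported, or that the cut-off will be carried forward. A useless marker would also be exposed by an AUC near 0.5.

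Much of this stands, and it limits the point. A reader might infer three stronger things that the document does not support:

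- *That reported accuracy in general will be inflated.* The only accuracy measure named is the AUC of CSI, which has no fitted coefficients. The choice among the triplicate readings rests on reliability and descriptive statistics, not on outcome. No discrimination measure is planned for the logistic model.
- *That the odds ratios will be seriously inflated.* With the four named terms the bias is about 9% on the log scale, and there is none if CSI has no effect. Section 6.3 lists further variables to capture, but does not say that all will enter the model.
- *That the protocol itself predicts 20 events.* The rate of almost 20% is for inductions in general, while this cohort is primiparous.

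The cut-off remains. Section 6.5 commits to seeking an optimum value in the whole cohort, and nothing in the protocol marks that value as provisional. The planned AUC interval tells the reader nothing about how stable the threshold is.

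**Conclusion.** The point holds for the cut-off. With 20 to 30 non-vaginal births, a Youden cut-off from this cohort has a 95% range of roughly 1.4 to 2.4 SD of CSI for true AUCs of 0.8 down to 0.6 (about 2 SD at 0.65). J reported at it would be too high by about 0.11 to 0.15 with 20 births and 0.09 to 0.13 with 30, and a marker with no value would show J of about 0.13 to 0.15.

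These sizes assume normally distributed CSI with equal spread in the two groups, the Youden criterion (the protocol names none), true AUCs of 0.5 to 0.8, and complete data. Exclusions under the complete-case rule can only reduce the number of births available. For the logistic model only a mild point is left: the covariate list is open, and bias grows from about 9% to about 20% on the log scale as terms go from 4 to 10.

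This is a cheap improvement to an exploratory analysis, and it does not invalidate the study.

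**What to change.** Amend section 6.5 as follows:

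1. Name the criterion for the optimum cut-off, for example the largest Youden index.
2. Report the cut-off with a bootstrap confidence interval.
3. Bootstrap the cut-off selection, and report optimism-corrected sensitivity and specificity beside the apparent values.
4. State that the cut-off is hypothesis-generating, and that the definitive study should be designed on the corrected values.
5. Replace the open list of covariates with CSI and the three pre-induction covariates already named: maternal age, gestational age and maternal weight at booking. Section 6.3 captures body mass index at booking and does not list weight, so state which one is meant.

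Penalised (Firth) estimation is optional, because the bias it would address is small with four terms.

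The cost is some extra programming and less favourable reported accuracy. No new data are needed and participants are not affected. The correction is incomplete: in a check with 20 non-vaginal births and a true AUC of 0.65, the bootstrap removed about 60 to 70% of the optimism in J. The corrected values should therefore be described as still somewhat favourable.

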**6.5.1 Participant Groups for Analyses**

Entire observational cohort of 100 women with singleton pregnancies undergoing induction of labour.

**6.5.2 Significance levels**

As this is an exploratory study no formal levels of significance are set. All statistics presented will be presented alongside 95% confidence intervals so as to give an indication of the level of precision only.

**6.5.3 Missing data**

The likelihood of missing data is small given the standard procedure in place to manage the study centrally. Final analyses will take place on a complete-case basis with no adjustments made (e.g. multiple imputation) in the case of missing data.

**6.5.4 Exposure to Intervention**

This is a non-interventional study.

**6.5.5 Trigger for Final Data Analyses**

Analysis of study data will take place once all participant data and samples have been received and processed; with corresponding laboratory data available for analysis.

**6.5.6 Data Descriptors**

Continuous data will be summarised as median, inter-quartile range and ranges. Categorical data shall be summarised as frequencies of counts and associated percentages.

**7. REGULATORY ISSUES**

**7.1 ETHICS APPROVAL**

Before the start of the study, a favourable opinion will be sought from the UK Health Departments Research Ethics Service NHS REC and the Health Research Authority for the study protocol, informed consent forms and other relevant documents.

The study will be submitted to the proposed research site for Confirmation of Capacity and Capability. The study will be conducted in accordance with the recommendations for physicians involved in research on human subjects adopted by the 18th World Medical Assembly, Helsinki 1964 and later revisions

**7.2 CONSENT**

Consent to enter the study must be sought from each participant only after a full explanation has been given, an information leaflet offered and time allowed for consideration. Signed participant consent should be obtained. The right of the participant to refuse to participate without giving reasons must be respected. After the participant has entered the study the clinician remains free to give alternative treatment to that specified in the protocol at any stage if he/she feels it is in the participant’s best interest, but the reasons for doing so should be recorded. In these cases the participants remain within the study for the purposes of follow‐up and data analysis. All participants are free to withdraw at any time from the protocol treatment without giving reasons and without prejudicing further treatment.

**7.3 CONFIDENTIALITY**

The Chief Investigator will preserve the confidentiality of participants taking part in the study and will abide by the Data Protection Act 2018 and the UK GDPR as amended from time to time and any successor legislation in the UK and any other directly applicable regulation relating to data protection and privacy. All members of the research team will have received ICH GCP training and are thus aware of the importance of patient confidentiality. Individual participant medical information obtained as a result of this study is considered confidential and disclosure to third parties is prohibited.

At time of consent participants will be allocated a unique participant identification number. A key to this information along with consent forms (containing patient identifiers) and pseudonymised CRFs (identified by participant identification number only) will be stored separately in locked filing cabinets, located in secure rooms within the CfWHR, UoL, with restricted keycard access to nominated clinical research/admin staff who work directly for the unit. Data from pseudonymised CRFs will be transferred to a password protected, nominated user restricted access REDCap database that will be housed on a secure server at the UoL. This server will be backed up and maintained in line with institutional compliance regulations for Data Protection and Information Security.

The study coordinator will consistently check that all study documentation stored in the CfWHR is pseudonymised and identifiable only by a unique study identification number (except for signed consent forms, which will be stored in a separate locked cabinet in the CfWHR).

The Chief Investigator will preserve the confidentiality of participants taking part in the study and will abide by the EU General Data Protection Regulation 2016 and Data Protection Act 2018.

**7.4 QUALITY ASSURANCE AND QUALITY CONTROL OF DATA**

Systems of quality assurance, including all elements described in this protocol have been/ will be implemented within relevant institutions with responsibility for this study. QC is applied to each stage of data handling to ensure that data are accurate, reliable and processed correctly.

The study site, facilities, laboratories and all data (including sources) and documentation must be available for GCP audit and inspection by competent authorities or IEC. Such audits / inspections may take place at any site where study related activity is taking place (the Sponsor’s site(s), the CfWHR or at any investigator’s site including laboratories).

The site staff should assist in all aspects of audit/inspection and be fully cognisant of the Sponsor communication strategy for single and multicentre studies. This includes management systems for the green light process prior to participant recruitment at site.

**7.5 RECORDS RETENTION**

The investigator at LWH site must make arrangements to store the essential study documents, (as defined in Essential Documents for the Conduct of a Clinical Study (ICH E6 (R2), Guideline for Good Clinical Practice)) including the Investigator Study File, until the Sponsor or the CfWHR informs the investigator that the documents are no longer to be retained.

In addition, the investigator is responsible for archiving of all relevant source documents so that the study data can be compared against source data after completion of the study (e.g. in case of inspection from authorities). The investigator is required to ensure the continued storage of the documents, even if the investigator, for example, leaves the clinic/practice or retires before the end of the required storage period. Delegation must be documented in writing. The CfWHR undertakes to store all electronic data related to completed database, except for source documents pertaining to the individual investigational site, which are kept by the investigator only. At the point where it is decided that the study documentation is no longer required; the Investigator will be responsible for the destruction of all site study specific documentation and the Sponsor /CfWHR will be responsible for the destruction of all study related materials retained.

Verification of appropriate informed consent will be enabled by the provision of copies of participants signed ICF being supplied to the CfWHR by LWH (recruiting site). This requires that name data will be transferred to the CfWHR, which is explained in the PIS. The CfWHR will preserve the confidentiality of participants taking part in the study and the UoL is a Data Controller registered with the Information Commissioners Office.

**7.6 STUDY DISCONTINUATION**

If this study is prematurely discontinued (e.g., due to safety) all participants must be informed and the reason for the discontinuation should be written on the end of study form for each participant. If a participant has been withdrawn completely from the study whilst the study is still ongoing, an end of study form should be completed.

**7.7 INDEMNITY**

The University of Liverpool professional indemnity and clinical trials insurance will apply as appropriate.

**7.8 SPONSOR**

The University of Liverpool.

**7.9 FUNDING**

Funded through the Harris-Wellbeing Preterm Birth Centre and the Centre for Women’s Health Research. Pregnolia AG provided the device for use in this study and provided financial aid to fund a Clinical Research Fellow to undertake the research.

Pregnolia AG and the study sponsor had no role in the study design and will not be involved in study management, data collection or analysis or subsequent publication.

**7.10 AUDITS**

The study may be subject to inspection and audit by regulatory bodies to ensure adherence to GCP and the UK Policy Framework for Health and Social Care Research (v3.2 10th October 2017).

**8. STUDY MANAGEMENT**

The day‐to‐day management of the study will be coordinated through the Centre for Women’s Health Research, Department of Women’ and Children’s Health.

**8.1 STUDY MANAGEMENT GROUP (SMG)**

A Study Management Group will be formed comprising the CI, other lead investigators / core study management staff who are central to the day-to-day running of the study. The SMG will be responsible for the day-to-day running and management of the study and will meet at regular intervals throughout the course of the study. The frequency of meetings will be decided by the CI. However it is expected that they should take place at least monthly. This group may consist of the following members of the core research team however all are not required to attend each meeting in person. Compulsory attendance in denoted by a *.

- *Chief Investigator
- Research Manager
- *Co-applicants
- Sponsor representative

**8.2 OVERSIGHT COMMITTEES**

This study will not convene both a Steering Committee or an Independent Safety and Data Monitoring Committee (ISDMC) as this is a low risk non-interventional prospective cohort study. Oversight will be provided by the SMG and Sponsor.

**9. END OF STUDY**

The study will end when the last recruited woman has delivered and both herself and her baby have been discharged from hospital, or 1 month after delivery, whichever is sooner and all planned analysis of collected data has taken place.

**10. MONITORING**

Central and study centre monitoring is conducted to ensure protection of participants in the study, and that procedures and data collection processes are of high quality and meet sponsor and, when appropriate, regulatory requirements. A risk assessment will be carried out to determine the level of monitoring required, and a subsequent monitoring plan will be developed to document who will conduct the central (and potentially site) monitoring, at what frequency monitoring will be carried out and the level of detail at which monitoring will be conducted.

A full quality control check of the protocol has been completed by the Centre for Women’s Health Research and the Chief Investigators. In addition, a SPIRIT (Standard Protocol Items: Recommendations for Interventional Trials) check has also been carried out in line with standard guidelines.

**10.1 RISK ASSESSMENT**

In accordance with the requirements of the Sponsor, a risk assessment has been completed in partnership with:

- Representatives of the Study Sponsors (University of Liverpool)
- Chief Investigator
- Members of the Study Management Group

In conducting this risk assessment, the contributors considered potential patient, organisational and study hazards, the likelihood of their occurrence and resulting impact should they occur. The outcome of the risk assessment is categorised based upon the potential risk associated with the study intervention in accordance with MRC/DH/MHRA Project on Risk-adapted Approaches to the Management of Clinical Trials:

<http://www.mhra.gov.uk/home/groups/l-ctu/documents/websiteresources/con111784.pdf>

- Type A: No higher than that of standard medical care
- Type B: Somewhat higher than that of standard medical care
- Type C: Markedly higher than that of standard medical care
- Non-CTIMP

**The initial risk assessment for this study resulted in a study category of Low Risk. This is a non-CTIMP.**

**10.2 SOURCE DATA**

Source data are all information, original records of clinical findings, observations, or other activities in a clinical study necessary for the reconstruction and evaluation of the study. Source data are contained in source documents (original records or certified copies). (ICH E6 (R2), 1.51).

